### Secondary outcomes

The secondary outcomes for this study will be:
HRQoL measured with the SF-36 (other than the MHS) at baseline and 12, 36, and 60 months after randomisation/baselineDisease remission 27 and 60 months after randomisation/baselineBiochemical disease control, defined as a normalised prolactin or actual pregnancy 12 months after randomisation/baselineRecurrence rate defined as recurrence of hyperprolactinaemia after achieving disease remission, measured 36 and 60 months after randomisation/baseline in all patients who were in remission at the 27-month follow-up time pointClinical symptom control, defined as the absence of clinical symptoms, registered in patient’s medical records and measured with the use of the National Cancer Institute Patient-Reported Outcomes version of the Common Terminology Criteria for Adverse Events (PRO-CTCAE) at 12, 27, 36, and 60 months after randomisation/baselineTumour shrinkage on MRI 12 and 36 months after randomisation/baselinePituitary functioning 12, 36, and 60 months after randomisation/baselineComplications of surgery registered in the patient’s medical records or side effects to DA treatment, measured with the PRO-CTCAE and a modified Impulse Control Disorder Questionnaire (ICD-Q), 12 and 36 months after randomisation/baselineDepression and anxiety scores, measured with the Hospital Anxiety and Depression Scale (HADS), 12 and 36 months after randomisation/baselineDisease burden, measured with the Leiden Bother and Needs Questionnaire (LBNQ), 12, 36, and 60 months after randomisation/baselineCost-effectiveness at 12 and 36 months after randomisation/baseline measured with the EQ-5D-5L 6, 9, 12, 18, 24, 27, 30, and 36 months after randomisation/baseline and the iMTA Productivity Cost Questionnaire (iPCQ) and the iMTA Medical Consumption Questionnaire (iMCQ) once every 6 months, starting 6 months after randomisation/baseline, until *T* = 36

### Sample size calculation

To detect a difference in remission rate at 36 months of 40% between surgery (expected rate 90%) and medical treatment (expected rate max. 50%), with a power of 0.8 and an *α* of 0.025, 55 patients per treatment group arm are needed, when considering that max. 30% in the interventional arm will not undergo surgery. However, to detect a difference of 10 points at the SF-36 mental health scale at *T* = 12 with an *α* of 0.025 and a power of 0.8, assuming that the standard deviation is 16, based on the general population [31], and that max. 30% of the interventional arm does not undergo surgery, at least 101 patients per treatment arm are needed. To compensate for the loss to follow-up, it is aimed to include 110 patients per treatment arm and therefore 220 patients in total per RCT/PRolaCT-O (aiming for at least 110 patients per treatment group in PRolaCT-O). If patient recruitment would prove challenging, and the required sample size for separate analyses of the RCTs cannot be reached for two or more of the RCTs (PRolaCT-1, PRolaCT-2, or PRolaCT-3) within the duration of the study, the planned analyses could be performed using the combined sample size for two to three RCTs of 220 patients.

### Planned statistical analyses

We intend to perform all statistical analyses separately for PRolaCT-O and PRolaCT-1, PRolaCT-2, and PRolaCT-3. However, a combined analysis of two to three RCTs may be performed, as stated above, using a regression analysis with adjustment for randomisation group type. A post hoc meta-analysis including all three RCTs and PRolaCT-O will be performed, whatever the course of the study.

To account for positive results due to multiple testing, a lower than usual *p*-value, i.e. < 0.02, will be considered statistically significant. All statistical analyses will be performed according to the intention-to-treat principle. In a sensitivity approach, a per-protocol analysis will also be performed, which may be of added value in case many patients, after consultation, decide not to be operated.

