##### Disease remission

In the three RCTs, the percentage of patients that achieve disease remission at 36 months will be calculated for the two treatment arms with corresponding 95% confidence interval and compared using a chi-square test.

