The study intervention in PRolaCT is thus the neurosurgical counselling rather than surgical intervention, which allows patients in the intervention groups to opt for surgery. If there is a substantial proportion of patients in the intervention group who do not undergo surgery, it would lead to an attenuation of found effects. Furthermore, as a part of standard care, participants in the control groups may still undergo surgery in the follow-up of the study (which is sporadically needed in case of severe DA intolerance or resistance). The expected cross-over between treatments was taken into account for the sample size calculation, resulting in a larger sample size needed. However, we anticipate that neurosurgical counselling greatly contributes to patients’ decision for a specific treatment, and therefore, our approach may decrease the risk of study drop-out due to disappointment over the outcome of randomisation.

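### Both primary endpoints are sized at alpha 0.025 but judged at p < 0.02, and the stated allowance for cross-over leaves out surgery in the control arm; this slightly lowers unadjusted power for MHS, not for remission

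*Protocol article*

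**What the plan says.** All references are to the protocol article.

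- **Sample size calculation.** Remission at 36 months is sized with power 0.8 and an alpha "of 0.025, 55 patients per treatment group arm are needed". MHS at 12 months is sized with an alpha "of 0.025 and a power of 0.8, assuming that the standard deviation is 16", and, given that "max. 30% of the interventional arm does not undergo surgery, at least 101 patients per treatment arm are needed". The recruitment target is 110 per arm, to cover loss to follow-up. The only departure from assigned treatment named here is non-surgery in the intervention arm.
- **Planned statistical analyses.** To allow for multiple testing, a p-value "i.e. < 0.02, will be considered statistically significant". The primary endpoints are not exempted. All analyses are by intention to treat.
- **Main endpoints.** MHS is analysed by linear regression with treatment and baseline MHS as covariates. The remission percentage in each arm is reported "with corresponding 95% confidence interval and compared using a chi-square test".
- **Control: standard care and Rationale for the study design.** Control patients may be offered surgery for intolerance of, or poor response to, the dopamine agonist. The Rationale calls this sporadic and continues: "The expected cross-over between treatments was taken into account for the sample size calculation, resulting in a larger sample size needed".

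**The concern.** A sample size delivers its stated power only for the test that will actually be used. Here the sizing assumes one significance level and the analysis section applies another to the same two endpoints. A primary p-value between 0.02 and 0.025 would meet the level the trial was sized for and still be declared non-significant. The 80% power quoted for MHS, the endpoint that drives recruitment, therefore belongs to a different rule from the one declared.

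The cross-over sentence raises a second, separate question. Under intention to treat, surgery in the control arm shrinks the between-arm difference just as non-surgery in the intervention arm does. The sentence comes straight after the one on control-arm surgery and speaks of cross-over between treatments, so it reads as covering both directions. If the sample size covers only one, the text claims more than the calculation contains.

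**Working it through.** **Inputs (Sample size calculation).** MHS difference 10, SD 16; remission 90% versus 50%; power 0.8; alpha 0.025; at most 30% of the intervention arm not operated. Allocation is 1:1 (Treatment allocation). The text does not say whether alpha is one- or two-sided.

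**Step 1: reproduce 101 for MHS.**
Diluted difference = 0.7 × 10 = 7.
Normal approximation: n = 2(z₁₋α/₂ + z₀.₈)² × 16² / 7².
At two-sided 0.025: 2 × (2.241 + 0.842)² × 256 / 49 = 99.3, so 100. The exact t calculation gives 100.6, so **101**, as stated. One-sided 0.025 gives 83, so the sizing is two-sided.

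**Step 2: reproduce 55 for remission.**
Diluted intervention rate = 0.7 × 0.90 + 0.3 × 0.50 = 0.78; control 0.50; mean 0.64.
n = [z₁₋α/₂ √(2 × 0.64 × 0.36) + z₀.₈ √(0.78 × 0.22 + 0.50 × 0.50)]² / 0.28².
At two-sided 0.025: (2.241 × 0.6788 + 0.842 × 0.6493)² / 0.0784 = 54.5, so **55**, as stated. One-sided 0.025 gives 45.

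Both figures thus come from two-sided 0.025, 30% non-surgery in the intervention arm, and no surgery in the control arm.

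**Step 3: apply the declared 0.02.**

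| | Two-sided 0.025 | Two-sided 0.02 |
|---|---|---|
| MHS, n per arm for 80% (t-test) | 101 | 107 |
| MHS, power at 101 per arm (t-test) | 80.2% | 77.7% |
| Remission, n per arm for 80% | 55 | 58 |
| Remission, power at 101 per arm | 97.7% | 97.1% |

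The alpha mismatch alone costs MHS 80.2 − 77.7 = 2.5 percentage points. If all 110 recruited per arm were evaluable, MHS power at 0.02 would be 81.5%, but the plan assigns those extra patients to loss to follow-up (implied loss 1 − 101/110 = 8.2%).

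**Step 4: control-arm surgery (assumed rates).** The documents give no rate. Let a fraction x of controls be operated and gain the full surgical effect. The MHS difference becomes 10 × (0.7 − x), and the control remission rate becomes 0.50 + 0.40x. At 101 per arm:

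| Assumed x | MHS difference | MHS power, 0.025 | MHS power, 0.02 | Remission power, 0.02 |
|---|---|---|---|---|
| 0 | 7.0 | 80.2% | 77.7% | 97.1% |
| 2% | 6.8 | 77.6% | 75.0% | 96.3% |
| 5% | 6.5 | 73.5% | 70.6% | 94.6% |

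Remission still has 90.6% power at an assumed 10%.

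**Step 5: the planned baseline adjustment.** The sizing takes no credit for it. With correlation ρ between baseline and month-12 MHS, the residual SD is 16√(1 − ρ²). At 0.02, 101 per arm and no control surgery (normal approximation, which gives 78.3% where the t-test gives 77.7%), power is 80.1% at ρ = 0.2 and 89.7% at ρ = 0.5. With 5% control surgery it is 79.5% at ρ = 0.4 and 84.3% at ρ = 0.5. The document states no ρ.

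**The case against.** The strongest reply is that the mismatch is small and in the conservative direction. The rule below 0.02 is the only decision rule in the article, and a sizing alpha does not compete with it. Two tests at 0.02 spend at most 4%, so false-positive control is not weakened. The planned MHS analysis adjusts for baseline, so the unadjusted 77.7% is not the power of the planned test. All of this stands, and it limits the point to a mismatch between stated power and stated rule. It does not remove the mismatch, because the plan quotes 80% at another alpha and states no correlation that would restore it.

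On cross-over, the sentence may mean only the 30% non-surgery, which is in the calculation. That 30% is a maximum: with 25% non-surgery and 5% control surgery, the difference is again 10 × (0.75 − 0.05) = 7. The 50% remission rate for medical treatment is also a maximum, above the 34% cited in the Background, and may leave room for cross-over. These are fair points about how much harm follows. They do not make the sentence accurate as it stands, because no control-arm rate enters either calculation.

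A reader might infer more than the documents support:

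- **Both endpoints are underpowered.** Remission has about 97% power at 101 per arm.
- **The 95% interval is a third test level.** It is attached to the remission percentage within each arm, so it is descriptive and sets no level for the comparison.
- **Control-arm surgery will be 5–10%.** The Background gives that range for more severe psychological side effects, not for surgery. The Rationale calls control surgery sporadic, and patients with severe side effects or resistant tumours are excluded at entry.
- **The threshold should cover eight tests, or Holm should be used.** Whether separate trials form one family is a matter of judgement, and Holm is a preference rather than the correction of an error.

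**Conclusion.** The point holds in a limited form. The sizing uses two-sided 0.025 and the analysis rule uses 0.02, so the 80% stated for MHS does not belong to the declared test. On the plan's own unadjusted inputs, MHS power at 101 evaluable per arm is 77.7%, and 80% would need 107. Remission is not affected in practice.

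The statement that cross-over was taken into account is borne out only for non-surgery in the intervention arm. Any further loss of MHS power from control-arm surgery rests on an assumed rate: 75.0% at 2% and 70.6% at 5%, at 0.02, if operated controls gain the full 10 points by month 12 and non-surgery reaches its 30% maximum. Baseline adjustment could offset some or all of this. A correlation just above 0.2 restores 80% without control surgery, and one between 0.4 and 0.5 does so with 5%. The documents establish neither the loss from control surgery nor the gain from adjustment.

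**What to change.** 1. **One alpha for the primary endpoints** in Sample size calculation and Planned statistical analyses. Two-sided 0.025 for each endpoint matches the sizing and keeps 2 × 0.025 = 5% over the two endpoints within each RCT. Alternatively, keep 0.02 and restate MHS power as about 78% (unadjusted, 101 evaluable per arm). If the covariance analysis is relied on to reach 80%, state the assumed baseline correlation.
2. **State that the alpha is two-sided**, as both sample sizes imply.
3. **Cross-over.** Either add an assumed control-arm surgery rate to Sample size calculation and restate power for both endpoints, or reword the sentence in Rationale for the study design so that it refers only to intervention-arm patients who do not have surgery.

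The cost is wording and restated figures, with no extra patients. Because moving from 0.02 to 0.025 relaxes the declared threshold in an unblinded trial, the choice should be made as a dated amendment before outcomes are compared between arms.

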### Treatment allocation

Within each RCT (PRolaCT-1, PRolaCT-2, or PRolaCT-3), participants are randomly allocated in a 1:1 ratio to either neurosurgical counselling (with potential subsequent surgery when desired) or standard care with DA. Randomisation is performed in blocks of sizes varying between 4, 6, and 8 patients and is stratified by sex to equally divide male participants and by tumour size (< 10 mm versus ≥ 10 mm). Randomisation is performed centrally in the LUMC using the built-in randomisation tool of the web-based database programme (Castor Electronic Data Capture (EDC), Castor, Amsterdam, the Netherlands). Investigators, treating physicians, and participants will not be blinded to the outcomes of randomization. With the use of varying block sizes, the allocation sequence is kept concealed by the randomisation programme. In PRolaCT-O, treatment choice, based on patient and physician preference, is solely recorded and may be DA treatment as a first- or second-line treatment, or surgical counselling as a second-line treatment (thus not in newly diagnosed patients). For all studies, the interpreters of MRIs, ophthalmologic assessments, and surgical difficulty will be blinded when possible. Unblinding will not occur.

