### Treatment

#### Intervention: surgical counselling

Participants who are randomised for the intervention group will receive extensive and personalised neurosurgical counselling by a neurosurgeon and an endocrinologist with specific expertise in pituitary care (preferably a combined consultation). All potential benefits and risks of surgery are discussed in a semi-standardised manner, offering both standardised information on surgical intervention and detailed expert opinion regarding the patient’s specific situation. This consultation may theoretically result in advising the patient to refrain from surgery during the shared decision-making process, despite the patient’s previous eligibility “on paper”. Moreover, based on information gathered during the counselling, the MDT may advise against surgery and propose standard treatment as a better alternative in this individualised approach. After counselling, the patient is asked for consent for surgery as is a standard preoperative requirement regardless of study participation. Participants in the intervention group may thus decide not to proceed with the surgical intervention. Participants who do not consent to surgery will continue the RCT in the intervention group, but receive treatment according to standard care. Patients receiving standard of care may be referred back to their own physician following the counselling.

When a participant and the MDT agree to surgery, an endoscopic transsphenoidal surgical resection of the prolactinoma is performed according to standard practice in an expertise centre. Patients are hospitalised for 2–5 days postoperatively. In the first weeks after discharge from the hospital, frequent contact by phone or visits to the outpatient clinic are needed to check for complications and recovery of the patient, according to the standards of care of the neurosurgical centre. The frequency of these visits is gradually reduced to (half-)yearly visits depending on the patient’s well-being.

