##### Combining the results of the different trials

Since the design of the three RCTs is similar, with the main difference being the duration of DA pre-treatment, the main results will be compared between the three RCTs and the PRolaCT-O study. We first compare the baseline characteristics between the studies. Then, a combined analysis including PRolaCT-O and the RCTs will be performed, using meta-analysis methods. If the results of the different studies differ substantially, we will explore if the differences can be explained by different patient populations in the different studies, using individual patient data (IPD) meta-regression methods, combined with inverse probability weighting.

Moreover, we will compare surgical outcomes between the intervention groups of the three RCTs, using a multivariate analysis, to compare the effects of the duration of DA pre-treatment on surgical outcomes.

In addition to the aforementioned analyses that will be performed according to the intention-to-treat principle, we will perform per-protocol analyses for both our primary and secondary endpoints.

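### A per-protocol analysis that serves its stated purpose would set operated intervention patients against an unselected control arm; add a complier-average effect and label per-protocol results descriptive

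*Protocol article*

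**What the plan says.** The protocol article, Planned statistical analyses, sets the main principle: "All statistical analyses will be performed according to the intention-to-treat principle". As a sensitivity approach it then adds that "a per-protocol analysis will also be performed, which may be of added value in case many patients, after consultation, decide not to be operated". The section Combining the results of the different trials widens the scope: "we will perform per-protocol analyses for both our primary and secondary endpoints".

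Three other places fix what following the protocol means in these trials:

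- Treatment allocation: "participants are randomly allocated in a 1:1 ratio to either neurosurgical counselling (with potential subsequent surgery when desired) or standard care with DA".
- Intervention: surgical counselling: "Participants who do not consent to surgery will continue the RCT in the intervention group, but receive treatment according to standard care". The same section says that, "based on information gathered during the counselling, the MDT may advise against surgery and propose standard treatment as a better alternative".
- Rationale for the study design: "The study intervention in PRolaCT is thus the neurosurgical counselling rather than surgical intervention". The same section explains that patients allocated to standard care are spared referral and neurosurgical counselling.

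The per-protocol set is not defined in the article, and no complier-average or instrumental-variable analysis is mentioned.

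**The concern.** A counselled patient who is not operated has followed the protocol, because counselling is the intervention. A per-protocol set that keeps such patients does nothing for the situation that the plan gives as its reason. A set that leaves them out removes a group formed after randomisation by preference and by clinical judgement. The matching patients in the control arm were never counselled, cannot be recognised and remain in the comparison.

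This matters because the hypothesis in the Background section is about resection, whereas ITT estimates the effect of offering counselling. A reader who wants the effect of surgery from the randomised data will turn to the per-protocol result. That result is most exposed to selection when many patients are not operated, which is the case for which the plan expects it to be useful.

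**Working it through.** **1. Possible per-protocol sets.**

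- Keep unoperated intervention patients: no selection, but also no answer to the stated purpose.
- Exclude them: a selected subgroup against an unselected control arm.
- Count them with the DA group (as treated): groups no longer formed by randomisation.
- Exclude them and also exclude operated controls: two selections on different grounds, since Control: standard care allows control-arm surgery for intolerance or insufficient response.

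No option both serves the purpose and keeps the randomised comparison.

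**2. The plan's own figures** (Sample size calculation). The inputs are a 10-point MHS difference, SD 16, at most 30% unoperated, alpha 0.025 and power 0.8. The diluted effect is 0.7 × 10 = 7 points. With two-sided alpha the normal formula gives 100 per arm and the t-based solution 100.6, hence the stated 101. For remission, 0.7 × 0.90 + 0.3 × 0.50 = 0.78 against 0.50 gives 55 per arm (two-sided, pooled variance, no continuity correction), as stated. Both figures reproduce on the ITT effect diluted by 30%.

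**3. Bias without baseline adjustment.** Let acceptors have mean m on DA, decliners m + g on DA, and let surgery add t in acceptors. Assume no surgery in controls and no effect of counselling alone.

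- Control mean: 0.7m + 0.3(m + g) = m + 0.3g.
- Operated intervention patients: m + t.
- Per protocol: t − 0.3g, so the bias is −0.3g.
- ITT: 0.7(m + t) + 0.3(m + g) − (m + 0.3g) = 0.7t.
- Complier-average effect: 0.7t / 0.7 = t, whatever g is.

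The documents do not give g. With t = 10 and g assumed at −10, −5, 0, +5 and +10, the per-protocol expectation is 13.0, 11.5, 10.0, 8.5 and 7.0. The complier-average effect is 10.0 throughout. A simulation of 8,000 trials per scenario with 101 per arm gave 9.9 to 10.1.

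**4. Bias under the planned model.** The main MHS analysis adjusts for baseline MHS. Assume the gap is the same at baseline and month 12, the SDs are equal and the correlation is r (not in the documents). The bias becomes 0.3 × |g| × (1 − r).

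- r = 0.3: 1.05 and 2.10 points for gaps of 5 and 10.
- r = 0.5: 0.75 and 1.50 points.
- r = 0.7: 0.45 and 0.90 points.

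The unadjusted per-protocol SE is 16 × √(1/70.7 + 1/101) = 2.48. At r = 0.5 it is 2.48 × √0.75 = 2.15. If surgery had no effect, the per-protocol test at the plan's 0.02 threshold would reject in about 2.8% and 5.3% of trials at r = 0.5. At r = 0.3 the figures are 3.3% and 7.6%, and at r = 0.7 they are 2.4% and 3.7%. Without any baseline adjustment they would be 4.4% and 13.2%.

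**5. Remission** (chi-square test, no adjustment stated). Hold controls at 50% and operated patients at 90%, so per protocol always shows 40 points. If decliners' remission on DA were 35%, acceptors' would be (0.50 − 0.3 × 0.35)/0.7 = 0.564. The true effect in acceptors would be 0.90 − 0.564 = 33.6 points, so per protocol is 6.4 too high. At 65% the true effect is 46.4, and per protocol is 6.4 too low. At 20% and 80% the error is 12.9 points in each direction, and at 50% it is zero. These decliner rates are assumptions.

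**6. Price of the complier-average effect.** The ITT SE is 16 × √(2/101) = 2.25. Divided by 0.7 it is 3.22, against 2.48 for per protocol (both unadjusted). If counselling alone moved decliners' MHS by 3 points, the estimate would shift by 0.3 × 3 / 0.7 = 1.3 points. If 10% of controls were operated, ITT would be 7 − 1 = 6. Then 6 / (0.7 − 0.1) = 10 is right, and 6 / 0.7 = 8.6 is not.

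**The case against.** The strongest reply is that the article does not define the per-protocol set, that such definitions belong in the SAP, and that this is one sensitivity analysis beside an ITT primary analysis. Much of this stands. Exclusion of unoperated patients is inferred from the stated purpose and is not written down. The plan also says only that the analysis may add value, acknowledges attenuation from non-uptake, and sizes the trials for it. What does not stand is that a definition would cure the problem: none of the options in step 1 meets the purpose and preserves randomisation.

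A reader might go further and infer four things that the documents do not support:

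- That the trials' own false-positive rate rises, for instance to 13%. That figure ignores the planned baseline adjustment, rests on an assumed 10-point gap, and concerns the per-protocol test only.
- That the analysis must favour surgery. The sign of the gap is unknown. MDT advice against surgery, which the article presents as a theoretical possibility, does not by itself imply worse remission on DA, and not everyone unoperated was so advised.
- That this is the programme's only evidence on surgery itself. Strong patient preference states that PRolaCT-O compares surgical and medical treatment, although observationally and with a propensity model for counselling.
- That a complier-average effect is free of bias. Participants are unblinded, MHS is self-reported and counselling is extensive. The 1.3-point shift in step 6 is similar in size to the per-protocol bias in step 4.

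**Conclusion.** The point holds as a limited one. For the purpose the plan gives it, the RCT per-protocol analysis gives up the randomised comparison, because unoperated patients can be identified and removed only in the intervention arm. The plan itself treats the same kind of factors (preference after counselling, likelihood of a good surgical result, DA side effects) as confounders that need weighting in PRolaCT-O.

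The size cannot be fixed from the documents. It is 0.3 times a residual gap that they do not give, and it is zero if that gap is zero. The MHS and remission ranges above rest on assumed gaps, on the planned maximum of 30% unoperated and, for MHS, on an assumed baseline correlation. The ITT primary analyses, their error rates and the sample size are untouched. What is at risk is any claim about surgery itself drawn from the per-protocol results.

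**What to change.** For both primary endpoints in the RCTs, add a complier-average causal effect as the main supplementary analysis of surgery itself. Use randomised arm as the instrument for surgery received, by month 12 for MHS and by month 36 for remission. Take the observed between-arm difference in surgery uptake as the denominator, so that control-arm surgery is counted, and not a fixed 0.7. Keep per-protocol tables if wanted, but label them descriptive and state which patients they exclude.

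State the two extra assumptions: no defiers, and no effect of counselling on outcome in patients whose surgery status it does not change. Vary the second for MHS, for example over −3 to +3 points in unoperated patients.

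The cost is analysis-plan wording. Treatment received is already monitored (Control: standard care), and the required sample size does not change. The price is a wider interval and an estimate that applies only to patients whose surgery depends on the allocation.
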